### **2.7.2 Demographic and medical data.**

Data to be extracted from the Sciensano database are a list of all nursing homes in Belgium with their RIZIV number, postal code, the capacity of each nursing home (number of beds), and suspected (CT and symptoms) and confirmed (PCR and AG POC test) COVID-19 related death rate.

At the NH level, the management will be asked, at baseline, about the proportion of care grade (according to the Katz evaluation scale) among their residents, if a COVID-19 vaccination campaign was organized in the NH yet (date, type of vaccine and vaccination coverage), the suspected and confirmed COVID-19 infection rate, the COVID-19 related and non-COVID-19 related death rate from the beginning of the crisis until now and if and when they had an outbreak (more than one COVID-19 infection that are suspected to be related). With every follow-up sampling timepoint, the NH will be asked about a vaccination campaign (when this did not take place yet at baseline), if COVID-19 testing was performed in their NH, the respective proportion of positive tests and COVID-19 related death rate.

Individual medical data, comprising medical history and if participants have experienced an episode of COVID-19 symptoms or underwent a COVID-19 (PCR/antigen) test (with mention of date and result) or if COVID-19 was confirmed by a CT-scan, reason of missing data of drop outs (death, hospitalisation, sick leave, leaving the job), and whether they received a COVID-19 vaccination (date, type of vaccine, number of doses) in both NH residents and staff will be collected through an online questionnaire at both baseline and follow-up sampling timepoints (LimeSurvey) (See Appendix 6.3 for questionnaires). The CRC will fill out the questionnaire concerning the resident participants during the week of the sampling timepoint. Therefore the head of the nursing staff or the representative of the resident can be asked to provide the data. In this questionnaire, the surveyed medical data will be linked to the participant identification code. Concerning the medical history, the participants (NH staff and residents) will be asked

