### **Secondary objectives**

4. To assess the seroprevalence according to vaccination status among NH residents and staff in Belgium at month 0 and at every follow-up visit in the cohort at month 2, 4, 6, 8 and 10.

The seroprevalence among NH residents and staff in Belgium at month 0, and follow-up in the cohort at month 2 (and if relevant at month 4, 6, 8, and 10), will be reported according to the vaccination status (Number of shots: 0, 1 or 2) and for the subgroups ‘with’ and ‘without’ a history of self-reported SARS-CoV-2 infection, averaged over NHs based on a GEE analysis with exchangeable covariance structure.

5. To assess the risk of getting a SARS-CoV-2 infection since vaccination between:
  - Residents and staff
  - Seropositive and seronegative participants at all timepoints
  - Individuals with or without previous self-reported SARS-CoV-2 infections
  - Adjusted for the updated vaccination degree of NH at all timepoints

For vaccinated participants only, a survival analysis will be performed to investigate the time (in days) to a SARS-CoV-2 infection since vaccination between sero-positive and -negative

participants at all time points. A participant is considered to have an event when the participant had a positive PCR test result (or a positive antigen rapid test, or a positive CT scan, or a positive saliva test in absence of a PCR test). The survival or censoring time (in days) is registered since 14 days after being fully vaccinated (full dose regimen) until first event (or censoring moment). If the proportional hazard assumption holds, a stratified (by NH) Cox proportional hazards regression model will be used to model the hazard of SARS-CoV-2 infection between sero-positive and -negative participants at all time points (modelled by the inclusion of a time-varying seropositivity status), adjusted for type of participant, history of self-reported SARS-COV-2 infections, and a time-varying NH vaccination degree. The analysis will be performed stratified by type of participant or other variables, if the proportional hazard assumption does not hold.

6. To assess the proportion of confirmed COVID-19 deaths and non-COVID-19 related deaths since vaccination and the time until death (within the study timeframe) between sero-positive and -negative participants for NH residents

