For vaccinated NH residents only, a survival analysis will be performed to investigate the proportion of deaths within the study follow-up and the time (in days) to a confirmed COVID-19 death since 14 days after being fully vaccinated (full dose regimen). The survival or censoring time (in days) is registered since 14 days after being fully vaccinated until first event (or censoring moment). A non-COVID-19 related death will be considered as a competing risk in the analysis. If the proportional hazard assumption holds, a stratified (by NH) Cox proportional hazards regression model will be used to model the cause-specific hazards between seropositive and seronegative residents. The latter will be included as a time-varying covariate. A history of self-reported SARS-COV-2 infections, a time-varying NH vaccination degree, province, age, gender, care profile, and presence of COVID-specific comorbidities will be

considered for model adjustment.

7. To assess the duration of SARS-CoV-2 specific antibody response (seroreversion/no antibody response) since 14 days after being fully vaccinated among NH residents and staff in Belgium.

The duration of SARS-CoV-2 specific antibody responses among NH residents and staff in Belgium will be modelled by means of an interval-censored survival analysis. Seroreversion will be defined as a negative rapid test result after at least one positive rapid test result or as two succeeding negative test results (implying the participant did not seroconvert after vaccination within two to four months). The time interval to seroreversion/no response is the time interval between 14 days after the (second) vaccination date (full dose regimen) and the first test moment of a negative test result after at least one positive rapid test or of the two succeeding negative rapid test results. As a sensitivity analysis, the event will also be defined as two succeeding negative rapid test results (whether or not after at least one positive rapid test result), if the rapid test result would turn out to be unstable.

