### **Tertiary objectives**

Although this study was not designed to assess vaccine effectiveness, end points will be compared between vaccinated and non-vaccinated participants, applying propensity score methods, if sufficient non-vaccinated participants occur in the random selected sample.

8. To assess the risk of getting SARS-CoV-2 infected between vaccinated and non-vaccinated (at last visit) residents/staff.

If a sufficient number of non-vaccinated participants are available in the sample, a survival analysis will be performed to investigate the time (in days) to a SARS-CoV-2 infection

since 14 days after being fully vaccinated between vaccinated and non-vaccinated participants. A participant is considered to have an event when the participant had a reported positive PCR test result (or a positive antigen rapid test, or a positive CT scan, or a positive saliva test in absence of a PCR test) during the baseline or one of the follow-up visits. The survival or censoring time (in days) is registered since 14 days after being fully vaccinated (or since 14 days after main (second) vaccination date in corresponding NH in case of non-vaccinated participants) until first event (or censoring moment).

If the proportional hazard assumption holds, a stratified (by NH) Cox proportional hazards regression model will be used to model the hazard of SARS-CoV-2 infection between staff and residents, and between vaccinated and non-vaccinated participants, adjusting for history of self-reported SARS-COV-2 infections, and a time-varying NH vaccination degree. Propensity score methods will be applied to reduce the effects of confounding. If insufficient non-vaccinated residents would be available in the cohort, the analysis will be performed for staff only.

9. To assess the proportion of confirmed COVID-19 deaths and non-COVID-19 related deaths and the time until death (within the study timeframe) between vaccinated and non-vaccinated residents.

If sufficient non-vaccinated residents would be available, a survival analysis will be performed to investigate the time (in days) to a confirmed COVID-19 death since 14 days after vaccination (or since 14 days after main (second) vaccination date in corresponding NH in case of non-vaccinated participants). A non-COVID-19 related death will be considered as a competing risk in the analysis.

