**Versie voor deelnemende medewerkers:**

1. Gelieve uw uniek studienummer in te vullen.
2. Neemt u nog deel aan de studie (zal deze vragenlijst vervolledigd worden) ?  
Zo neen, waarom niet?

*Door de onderzoeker in te vullen*

- a. Tussentijdse afwezigheid in de studie (ziekte, vakantie, hospitalisatie ...)
- b. Deelnemer wenst niet meer deel te nemen
- a. Vermoedelijk of bewezen COVID-19 overlijden                      datum van overlijden:
- b. Niet-COVID-19 gerelateerd overlijden                      datum van overlijden:
- c. Medewerker is niet langer werkzaam in het WZC

*Vraag 3 wordt enkel toegevoegd indien voordien neen werd geantwoord.*

3. Bent u gevaccineerd tegen COVID-19?
  - a. Ja, 1 dosis
  - b. Ja, 2 dosissen
  - c. Neen
  - d. Zo ja, welk vaccin kreeg u toegediend
    - i. Het AstraZeneca/Oxford vaccin
    - ii. Het BioNtech-Pfizer vaccin
    - iii. Het Moderna vaccin
    - iv. andere
  - e. Zo ja, datum van vaccinatie (eerste spuit).
4. Bent u in de afgelopen twee maanden getest geweest op het coronavirus (via PCR/ag-sneltest/of radiologisch via CT-scan)? Ja/Nee
5. Zo ja. Bent u in de afgelopen 2 maanden (tussen de vorige testronde en nu) positief getest?  
*Meerdere antwoordmogelijkheden*
  - Ja, via PCR-test (test waarbij men via een neuswisser een staal afneemt en u na labo-analyse het resultaat krijgt)
  - Ja, via antigeen sneltest (test waarbij men via een neuswisser een staal afneemt en men binnen het kwartier het resultaat kan aflezen)
  - Ja radiologisch, via een CT-scan
  - neen
6. Zo ja, datum van 1ste positieve PCR-test of sneltest in de afgelopen 2 maanden (bij benadering)?

7. Indien COVID-19 radiologisch bevestigd werd via een CT-scan , vermeld de datum van deze CT-scan.
8. Hebt u in de afgelopen 2 maand (tussen de vorige testronde en nu) een periode 1 of meerdere van volgende symptomen ervaren, zonder dat hier een duidelijke verklaring voor was? Duid aan wat van toepassing is (meerdere antwoordmogelijkheden).
  - Hoest
  - Kortademigheid
  - Pijn op de borst
  - Smaakverlies
  - Geurverlies
  - Verergering van chronische respiratoire aandoeningen (vb. COPD, astma, chronische hoest,...)
  - Koorts
  - Spierpijn
  - Vermoeidheid
  - Loopneus/verstopte neus
  - Keelpijn
  - Hoofdpijn
  - Verlies van eetlust
  - Diarree
  - Acute verwardheid
  - Plotse val
9. Zo ja, wanneer hebt u, bij benadering, deze symptomen ervaren? Gelieve de dag aan te geven waarop deze symptomen zijn begonnen.

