### **Version pour les résidents participants**

(à remplir par l'examineur; à demander par l'infirmière ou l'infirmière en chef ou le représentant du résident):

12. Veuillez saisir le numéro d'étude unique du participant.

13. Le résident participe-t-il toujours à l'étude (ce questionnaire sera-t-il rempli)? Oui Non

Si non, pourquoi pas?

- a. Décès COVID présumé ou prouvé (date du décès)
- b. Décès non lié au COVID-19 (date du décès)
- c. Le résident ne souhaite plus participer

*La question 14 n'est ajoutée que si la réponse était non auparavant.*

14. • Le participant a-t-il été vacciné contre le COVID-19?

o Si oui, quel vaccin le participant a-t-il reçu

- ☐ Le vaccin AstraZeneca / Oxford
- ☐ Le vaccin BioNtech-Pfizer
- ☐ Le vaccin Moderna

o Si oui, date de vaccination (première seringue).

15. Le participant a-t-il été testé pour le coronavirus (via PCR / test rapide ag / ou radiologiquement via CT scan) au cours des deux derniers mois? Oui Non

16. Si c'est le cas. Le participant a-t-il été testé positif pour le coronavirus au cours des 2 derniers mois (entre le cycle de test précédent et maintenant)?

- Oui, via un test PCR (test dans lequel un échantillon est prélevé via un écouvillon nasal et vous obtenez le résultat après analyse en laboratoire)
- Oui, via un test rapide d'antigène (test dans lequel un échantillon est prélevé via un tampon nasal et le résultat peut être lu en 15 minutes)
- Oui, radiologiquement, via un scanner
- Non

17. Si oui, date du 1er test PCR positif ou test rapide au cours des 2 derniers mois (approximative)?

18. Si le COVID-19 a été confirmé radiologiquement par un scanner, indiquez la date à laquelle cela s'est produit.

19. Le participant a-t-il ressenti un ou plusieurs des symptômes suivants au cours des 2 derniers mois (entre le cycle de test précédent et maintenant), sans aucune explication claire à ce sujet? Indiquez ce qui s'applique (options de réponses multiples).

- Toux
- Essoufflement
- Douleur thoracique
- Perte de goût
- Perte d'odeur
- Aggravation des maladies respiratoires chroniques (ex: BPCO, asthme, toux chronique, ...)
- Fièvre
- fatigue musculaire
- Fatigue
- Nez qui coule / bouché
- Gorge irritée
- Mal de crâne
- Perte d'appétit
- La diarrhée
- Confusion aiguë
- Chute soudaine

20. Si oui, quand le participant a-t-il ressenti ces symptômes? Veuillez indiquer le jour où ces symptômes ont commencé.

21. Le cas échéant, le participant a-t-il été vacciné avec un vaccin contre le COVID-19?  

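### The questionnaires hold no labelled second-dose date and do not ask dose number again after 'one dose', so time zero of the vaccinated-cohort analyses is not observed per participant

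*Protocol*

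**What the plan says.** Objective numbers below are those of section 3.2.

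**What the analyses use.** For infection after vaccination (objective 5): "The survival or censoring time (in days) is registered since 14 days after being fully vaccinated (full dose regimen) until first event". For death in vaccinated residents (objective 6): "The survival or censoring time (in days) is registered since 14 days after being fully vaccinated until first event". For duration of the antibody response (objective 7), time runs over "the time interval between 14 days after the (second) vaccination date (full dose regimen") and the visit that shows the event. Objective 8 uses the same origin for vaccinated participants. Objective 9 says 14 days after vaccination without naming the dose. For the unvaccinated group both count "since 14 days after main (second) vaccination date in corresponding NH in case of non-vaccinated participants". Objective 4 reports seroprevalence by 0, 1 or 2 shots.

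**What the text promises.** Section 2.7.2 says that "whether they received a COVID-19 vaccination (date, type of vaccine, number of doses) in both NH residents and staff will be collected", at baseline and at follow-up.

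**What the forms ask.** The date field in the main vaccination question reads "Zo ja, datum van vaccinatie (eerste spuit"), that is, the first injection. The wording is equivalent on the resident forms and in French. The Dutch follow-up forms carry the rule "Vraag 3 wordt enkel toegevoegd indien voordien neen werd geantwoord". The French resident follow-up form says "La question 14 n'est ajoutée que si la réponse était non auparavant", and the French staff form has the same rule for its question 20.

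**The concern.** A survival analysis needs an origin for each person. Here the origin is tied to completion of the regimen, and the only labelled date is that of its start. The date of completion decides who enters the vaccinated cohort, which infections and deaths count, and how long antibodies are said to have lasted. If the origin is set too early, person-time before full vaccination is counted as after it. If it is set too late, early events are lost.

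An answer of one dose is a 'yes', so the question that records dose number does not come back for that person. In objective 4 such a participant can remain in the one-shot group at later visits after receiving a second dose. A SAP can add an imputation rule, but it cannot supply a date or dose count that was never collected.

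**Working it through.** The plan states no figure on this point, so the main check sets the data each analysis needs against every vaccination item in Appendix 6.3.

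| Needed (section 3.2) | Individual forms | Nursing-home form |
|---|---|---|
| Number of shots at each visit (objective 4) | Asked at baseline on all forms. At follow-up asked only after an earlier 'no'. The French resident follow-up form has no one-dose/two-dose options | Home totals only |
| Date the regimen was completed (objectives 5 to 7; vaccinated group in 8 and 9) | First-injection date. A closing follow-up item asks for one vaccination date, dose not named | Second-round date, not asked again after an earlier 'yes' |
| Main second-round date (unvaccinated group in 8 and 9) | Not applicable | As above |
| Time-varying vaccination degree of the home (objectives 5, 6, 8, 9) | Not applicable | Coverage counts, not asked again after an earlier 'yes' |

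The closing items are number 10 (Dutch staff), 11 (Dutch residents), 28 (French staff) and 21 (French residents). They carry no 'only after no' rule, but are to be introduced only once applicable. A person with two doses could enter either date. The one-off staff hesitancy item merges one and two doses and asks for no date.

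**By type of participant, two-dose regimen**

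- *Two doses at baseline.* Completion is known. Its date must be inferred from the home's second-round date or from an assumed interval after dose 1.
- *One dose at any visit.* The dose question does not return. Completion and its date rest on the unlabelled closing item, or on a home second-round date if one was recorded. A home that had held only round 1 at baseline has answered 'yes' and need not report round 2.
- *'No', then two doses at a later visit.* Dose 2 lies between the first-injection date and that visit. With visits at 60-day steps and a margin of 7 days, the first gap between visits is 60 − 7 = 53 to 60 + 7 = 67 days. Later gaps are 60 − 14 = 46 to 60 + 14 = 74 days if both visits use their full margins.

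A participant whose full regimen is a single dose is not affected, because the first-injection date is then the completion date.

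**Size, under a stated assumption.** The documents give no dose interval. Assume 3 to 12 weeks, that is 21 to 84 days.

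- Time zero falls 21 + 14 = 35 to 84 + 14 = 98 days after dose 1.
- Spread if the interval is wholly unknown: 98 − 35 = 63 days.
- Share of follow-up: 63 / 300 = 21%.

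The spread is close to the 60-day visit spacing. In objective 7 the event time is already known only to within a visit interval, so an uncertain origin adds a second unknown of similar width.

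**Who is affected.** The table of changes reports 15% of staff unvaccinated in the first round, so about 100 − 15 = 85% had at least one dose. It does not split one dose from two and gives no resident figure. The campaign began on 5 January 2021 and Table 1 marks the first collection in February 2021. For a home vaccinated on the first day, the assumed interval puts dose 2 between 26 January (day 21) and 30 March (day 84). People between doses at baseline are therefore plausible, but their share cannot be derived.

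**The case against.** The best defence is that the information is spread over several places rather than missing. Each individual follow-up form ends with a second vaccination-date item that is open to everyone. The home questionnaire asks for first-round and second-round dates, and the protocol itself trusts the home's second-round date enough to use it as time zero for unvaccinated participants. Product is recorded, so a product-specific interval could be used. Section 2.7.2 states the right intention, which makes this a mismatch between form and text. Only the French resident follow-up form lacks the dose options, and only residents who previously answered 'no' see that question.

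Much of this stands, and it rules out three stronger readings that a reader might infer:

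- *That the forms stop asking about vaccination after any 'yes'.* They do not, because the closing items remain. What is not asked again is the number of doses.
- *That time zero cannot be built.* An approximate origin can be built for many participants from home dates.
- *That the error equals the dose interval itself, 21/300 = 7% to 84/300 = 28% of follow-up.* With imputation the error is the true interval minus the assumed one, so that ratio does not measure it.

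The defence does not close the gap. The closing item does not say which dose it dates. The home's second-round date is dropped after an earlier 'yes', and even when present it does not show whether or when a given person received dose 2.

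**Conclusion.** The point holds as a contradiction between section 2.7.2 and the forms in Appendix 6.3. For participants on a two-dose regimen, the origin of objectives 5 to 7 and of the vaccinated group in objectives 8 and 9 is not observed individually and would need an imputation that the protocol does not describe. For objective 9 this assumes that vaccination there also means the full regimen. The dose classification in objective 4 can be out of date for anyone first recorded with one dose. The gated home coverage counts also leave the time-varying vaccination degree without updates.

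The 63-day spread (21% of 300 days) rests on the assumed 3 to 12 weeks and on knowing nothing more about the interval. Using product or home dates would narrow it. The number of participants affected cannot be stated from the document.

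The primary objectives do not use vaccination dates and are untouched. Objectives 8 and 9 are conditional on enough unvaccinated participants. Within the secondary objectives the gap should be closed, because it lies in what is collected.

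**What to change.** Amend Appendix 6.3 so that it delivers what section 2.7.2 promises:

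- At each visit until the regimen is complete, ask every participant for the number of doses received and the product and date of each dose. Replace the 'only if previously no' rule on the individual forms accordingly.
- Merge the closing items (staff 10, residents 11, French 28 and 21) into this question, or label which dose they date.
- Use the same response options in Dutch and French, including dose number on the French resident follow-up form.
- Ask each home for its second-round date and its vaccination coverage at every visit, and adjust the matching sentence on the home questionnaire in section 2.7.2.
- Back-fill second-dose dates once for everyone already enrolled, for example from the homes' own vaccination records.
- If dates still remain missing, state the imputation rule for time zero before analysis.

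The cost is a questionnaire amendment, a slightly longer form and a one-off back-fill. No new study procedure is needed.

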### **4.3 Bias and limitations**

- Loss of follow-up or missing data is possible, for instance, when a NH staff-member is not present at the moment of sample collection or a sample was not collected due to heavy workload. In this case, effort will be made to contact the NH and collect the sample within two days after the sampling day. In case of, for instance hospitalization of NH resident or self-isolation of NH staff, missing test result data is inevitable. In order to prevent missing data in the online questionnaires, results will be monitored and effort will be made to remind participants to fill in the survey (by e-mail/telephonic contact or at the moment of testing).

- Underestimation of the presence of SARS-CoV-19 seroprevalence among this population due to:

- Testing method limitations, however, the COVID-19 IgG/IgM Rapid Test Cassette (Orient Gene Biotech Co.) provides good sensitivity (92,9%) and specificity (96,3%) (Sciensano, 2020).
- Data collection, however, researchers/CRC's in charge of collecting the samples will be trained to ensure correct use of the COVID-19 IgG/IgM Rapid Test Cassette and interpretation of the results to minimize reporting bias.

- Due to practical limitations, seroprevalence data cannot be collected at the same point in time in all participants in this study. Seroprevalence, however, is subjected to fluctuations of the infection rate in the current SARS-CoV-2 pandemic and is therefore also time-dependent. Therefore, the maximal difference between the first and last samples collected within the baseline collection round is set at  $\pm 4$  weeks days.

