### **Versie voor deelnemende bewoners**

*(in te vullen door de onderzoeker; bevragen bij de (hoofd)verpleegkundige of de vertegenwoordiger van de bewoner):*

1. Gelieve het uniek studie nummer van de deelnemer in te vullen.
2. Neemt de bewoner nog deel aan de studie (zal deze vragenlijst vervolledigd worden)?  
ja/neen  
Zo neen, waarom niet?
  - a. Vermoedelijk of bewezen COVID-overlijden (datum overlijden)
  - b. Niet-COVID-19 gerelateerd overlijden (datum overlijden)
  - c. Bewoner wenst niet meer deel te nemen

*Vraag 3 wordt enkel toegevoegd indien voordien neen werd geantwoord.*

3. Is bewoner gevaccineerd tegen COVID-19?
  - a. Ja, 1 dosis
  - b. Ja, 2 dosissen
  - c. Neen
  - d. Zo ja, welk vaccin werd toegediend
    - i. Het AstraZeneca/Oxford vaccin
    - ii. Het BioNtech-Pfizer vaccin
    - iii. Het Moderna vaccin
    - iv. andere
  - e. Zo ja, datum van vaccinatie (eerste spuit).
- 4.

5. Is de deelnemer in de afgelopen twee maanden getest geweest op het coronavirus (via PCR/ag-sneltest/of radiologisch via CT-scan)? Ja/Nee
6. Zo, ja. Is de deelnemer in de afgelopen 2 maand (tussen de vorige testronde en nu) **positief** getest op het coronavirus?
  - Ja, via PCR-test (test waarbij men via een neuswisser een staal afneemt en u na labo-analyse het resultaat krijgt)
  - Ja, via antigen sneltest (test waarbij men via neuswisser een staal afneemt en men binnen het kwartier het resultaat kan aflezen)
  - Ja, radiologisch, via een CT-scan
  - Neen
7. Zo ja, datum van 1ste positieve PCR-test of sneltest de voorbije 2 maanden (bij benadering)?
8. Indien de COVID-19 radiologisch bevestigd werd via een CT-scan, vermeld de datum waarop dit is gebeurd.
9. Heeft de deelnemer in de afgelopen 2 maand (tussen de vorige testronde en nu) een periode 1 of meerdere van volgende symptomen ervaren, zonder dat hier een duidelijke verklaring voor was? Duid aan wat van toepassing is (meerdere antwoordmogelijkheden).
  - Hoest
  - Kortademigheid
  - Pijn op de borst
  - Smaakverlies
  - Geurverlies
  - Verergering van chronische respiratoire aandoeningen (vb. COPD, astma, chronische hoest,...)
  - Koorts
  - Spierpijn
  - Vermoeidheid
  - Loopneus/verstopte neus
  - Keelpijn
  - Hoofdpijn
  - Verlies van eetlust
  - Diarree
  - Acute verwardheid
  - Plotse val
10. Zo ja, wanneer heeft de deelnemer, bij benadering, deze symptomen ervaren? Gelieve de dag aan te geven waarop deze symptomen zijn begonnen.

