#### **Version pour les employés participants:**

18. Veuillez saisir votre numéro d'étudiant unique.
19. Participez-vous toujours à l'étude (ce questionnaire sera-t-il rempli)?

Sinon, pourquoi pas?

*À compléter par le chercheur*

- c. Absence provisoire de l'étude (maladie, vacances, hospitalisation ...)
- d. Le participant ne souhaite plus participer
- a. Mort suspectée ou prouvée de COVID-19 Date de décès:
- b. Décès non liés au COVID-19 Date de décès:
- c. L'employé ne travaille plus au WZC

*La question 20 n'est ajoutée que si la réponse était non auparavant.*

20. Avez-vous été vacciné contre le COVID-19?

- Oui, une dose
- Oui, deux doses
- Non

- o Si oui, quel vaccin vous a-t-il administré
    - ☐ Le vaccin AstraZeneca / Oxford
    - ☐ Le vaccin BioNtech-Pfizer
    - ☐ Le vaccin Moderna
    - ☐ autre
  - o Si oui, date de vaccination (première seringue).
- 21.
22. Avez-vous été testé pour le coronavirus (via PCR / test rapide AG / ou radiologique via CT scan) au cours des deux derniers mois? Oui Non
23. Si c'est le cas. Avez-vous été testé positif au cours des 2 derniers mois (entre le cycle de test précédent et maintenant)? Plusieurs options de réponse
- Oui, via un test PCR (test dans lequel un échantillon est prélevé via un écouvillon nasal et vous obtenez le résultat après analyse en laboratoire)
  - Oui, via un test rapide d'antigène (test dans lequel un échantillon est prélevé via un tampon nasal et le résultat peut être lu en 15 minutes)
  - Oui radiologiquement, via un scanner
  - non
24. Si oui, date du 1er test PCR positif ou test rapide au cours des 2 derniers mois (approximative)?
25. Si le COVID-19 a été confirmé radiologiquement par un scanner, indiquez la date de ce scanner.
26. Au cours des 2 derniers mois (entre la précédente série de tests et maintenant), avez-vous ressenti un ou plusieurs des symptômes suivants pendant une période, sans aucune explication claire? Indiquez ce qui s'applique (options de réponses multiples).
- Toux
  - Essoufflement
  - Douleur thoracique
  - Perte de goût
  - Perte d'odeur
  - Aggravation des maladies respiratoires chroniques (ex: BPCO, asthme, toux chronique, ...)
  - Fièvre
  - fatigue musculaire
  - Fatigue
  - Nez qui coule / bouché
  - Gorge irritée
  - Mal de crâne
  - Perte d'appétit
  - La diarrhée
  - Confusion aiguë
  - Chute soudaine

27. Si oui, quand avez-vous ressenti ces symptômes? Veuillez indiquer le jour où ces symptômes ont commencé.

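### After an uncompleted follow-up form, mainly a staff one, the next form does not ask about the skipped interval; separately, no individual form records the saliva tests that count as events

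*Protocol*

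**What the plan says.** **Look-back window.** In the Dutch staff follow-up form (section 6.3), question 4 is a filter on having been tested in the past two months: "Bent u in de afgelopen twee maanden getest geweest op het coronavirus". Question 5 asks those who answer yes whether they tested positive, and adds in brackets that the period meant is the one since the previous round: "Bent u in de afgelopen 2 maanden (tussen de vorige testronde en nu) positief getest". Question 6 asks for the date of the first "positieve PCR-test of sneltest in de afgelopen 2 maanden (bij benadering". The symptom item uses the same window. The Dutch resident form repeats it ("Is de deelnemer in de afgelopen 2 maand (tussen de vorige testronde en nu"), and so do the French forms ("Avez-vous été testé positif au cours des 2 derniers mois (entre le cycle de test précédent et maintenant" for staff).

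**Uncompleted forms.** Question 2 of the staff form asks whether this questionnaire will be completed. If not, the researcher ticks a reason, one of which is "Tussentijdse afwezigheid in de studie (ziekte, vakantie, hospitalisatie". No test, result or date is attached to that option. The resident form has no such option; its reasons are death or withdrawal.

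**Use of the answers.** In section 3.2, the event in objectives 5 and 8 is a positive PCR test, or a positive antigen rapid test, a positive CT scan or "a positive saliva test in absence of a PCR test". Objective 8 adds that the positive result is one reported at baseline or at a follow-up visit.

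**The concern.** Infection is itself a reason to be absent. Section 4.3 foresees this for the antibody sample: "In case of, for instance hospitalization of NH resident or self-isolation of NH staff, missing test result data is inevitable". Section 2.5 likewise lists sick leave for staff and hospitalisation for residents among the causes of drop-out. If an infected staff member's form is left uncompleted for that round, the infection falls in the interval before the missed round. The next form does not ask about that interval.

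The loss would therefore be related to the outcome. It would also be uneven, because the temporary-absence option exists only on the staff form. Residents versus staff is the first contrast named in objective 5, and objective 8 is to be run in staff alone if too few residents are unvaccinated. An answer that was never requested cannot be recovered at the analysis stage.

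The saliva mismatch is a different fault. It applies at every round, whether or not a form was missed.

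**Working it through.** The plan gives no figure for this point, so the check compares the visit schedule with the look-back window.

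**Inputs**
- Rounds at days 0, 60, 120, 180, 240 and 300, with a margin of ±7 days (section 2.4).
- Look-back of two months, taken as 60 to 61 days (section 6.3, follow-up forms).

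**One form missed**
- Nominal time between completed forms: 2 × 60 = 120 days.
- With margins at both ends: 120 − 14 = 106 to 120 + 14 = 134 days.
- Time not asked about = time between completed forms − look-back.
- Nominal: 120 − 61 = 59 to 120 − 60 = 60 days, about half of the 120.
- Lower limit: 106 − 61 = 45 days (45/106 = 42%).
- Upper limit: 134 − 60 = 74 days (74/134 = 55%).
- An infection shortly before the missed round lies in this uncovered part.

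**No form missed**
- Consecutive rounds can be up to 60 + 14 = 74 days apart, so a literal two months falls short by up to 74 − 61 = 13 to 74 − 60 = 14 days.
- The bracketed gloss in question 5 removes this shortfall for a respondent who follows it. The gloss is not in the filter, question 4.

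**Where it can occur.** There are five follow-up rounds. A missed month-10 form has no later form, so that case is loss to follow-up and not a look-back fault. Four of the five intervals can be affected.

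**Other sources in the protocol**
- The nursing-home follow-up form collects only aggregate counts of positives.
- The reason for a missed antibody test is documented (section 2.7.3), but without a virus test result or date.
- The rapid antibody test taken on return is not part of the event definition.

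None of these supplies an individual, dated positive test.

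**Saliva.** The positive-test items on the individual forms, at baseline and follow-up, in Dutch and French, for staff and residents, offer PCR (described as a nasal swab), antigen rapid test (also a nasal swab), CT scan, or no. None offers saliva.

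**After the fix.** If the window starts at the last completed questionnaire, the uncovered time after a missed form falls from about 60 days to 0.

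**The case against.** The strongest reply is that a missed finger-prick is not a missed questionnaire. The statement in section 4.3 about inevitable missing data concerns the antibody sample. The same paragraph treats the questionnaires separately: they are online, monitored, and followed up by e-mail, by telephone or at testing. An isolating staff member can report the infection in the very round whose blood test was missed. This stands, so a reader who infers that such infections are never recorded goes too far. The gap opens only when the form itself is left uncompleted, which question 2 of the staff form explicitly allows.

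The second reply concerns residents, who are 1656 of the 3036 participants. The researcher completes their form from the head nurse or representative, so the resident need not be present, and no temporary-absence option exists. This also stands. The resident form shares the narrow window, but nothing shows that resident forms would be skipped.

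Third, a reader might infer that a returning participant is analysed as event-free over the uncovered interval. The protocol does not say so. Follow-up runs to first event or to a censoring moment that is not defined here, and its definition may properly sit in a statistical analysis plan.

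Fourth, a respondent might read the previous round as their own last round. That is possible, but the words *past two months* in the same question point the other way.

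On saliva, a respondent might tick PCR for a saliva sample analysed by PCR. The form describes PCR as a nasal swab, however, and section 3.2 lists saliva as a separate test used when there is no PCR, so the mismatch remains.

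**Conclusion.** The point holds in a limited form. When a follow-up questionnaire is not completed, mainly for staff marked temporarily absent, the next form leaves about 60 of 120 days unasked (45 to 74 with the visit margins). Any infection that caused the absence lies in that part. The expected direction is fewer recorded infections, more so in staff, in secondary objective 5 and tertiary objective 8. The direction for other contrasts, such as vaccinated versus unvaccinated, is not established, because the protocol gives no absence rates by group.

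The share of infections lost cannot be computed. A reader might assume 10 to 14 days of isolation, subtract the two-day recovery period, and arrive at (10 − 2)/60 = 13% to (14 − 2)/60 = 20% of staff infections. The protocol does not support this. It gives no isolation length and no rate of uncompleted forms. The calculation needs every isolating person to leave an online form blank and then return. The two days are the window for recovering the antibody test, not a questionnaire deadline.

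Both primary objectives rest on rapid antibody results and are untouched. Objective 8 is also conditional on enough unvaccinated participants. The saliva mismatch is certain, but its size is unknown too. Overall this is a minor point and a cheap improvement.

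**What to change.** In the Dutch and French individual follow-up forms, for staff and residents:
- Replace the two-month window with *since your last completed study questionnaire on [pre-filled date]*. Apply it to the filter on testing, the positive result with its date, and the symptoms.
- Add saliva as a test type, so that the forms match the event definition in section 3.2.

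In the survival analyses for objectives 5 and 8, censor at the last completed questionnaire where an interval remains uncovered. This is a fallback only: if infection caused the absence, that censoring is itself related to the outcome, so the change to the forms should come first.

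The cost is a wording change and a date carried forward from the survey database. The table of changes shows that the follow-up questionnaire was already amended once after the first round. The only downside is a slightly longer recall period for those who missed a form.
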